### Material

At T0 handedness (39), disease duration, medication dosage intake per day, the Montreal Cognitive Assessment test [MoCA, (40)] are assessed. The MoCA is divided into visuo-spatial abilities, short-term memory, executive function, attention and working memory, language and phonemic fluency, and orientation.

Parkinsonian motor symptoms are assessed by the Movement Disorders Society unified Parkinson's Disease Rating Scale (MDS-UPDRS) subscale III (41) at T0, T1, and T2. Severity of the upper limb motor deficits is measured with the items 3.3 to 3.6 and 3.15 to 3.18 of the MDS-UPDRS subscale III.

### Primary Endpoint

The DextQ-24 is assessed at T0, T1, and T2, which is a standardized patient self-rated outcome measure for evaluating dexterity related ADL in PD (4). This questionnaire contains 24 questions, which are divided into five subgroups (“washing/grooming;” “dressing;” “meals and kitchen;” “everyday tasks;” “TV/CD/DVD”). For each question, patients must state whether they have no problems (1 point), minor problems (2 points), major problems (3 points), or need aid (4 points) to perform the task. Points are added in each subgroup and summed to a total score. Score ranges from a minimum of 24 to a maximum of 96 points.

### Secondary Endpoints

The Nine Hole Peg test (9-HPT) and the coin rotation (CR) task are used to explore hand and finger function at T0, T1, and T2. The 9-HPT is a standardized, well established, and reliable measure of hand performance in patients with PD (42, 43). The patients have to take nine pegs one by one into the holes on a board and then move them back to the container. The CR task (44) measures fine coordinated finger movements and has proven to be a suitable and valid dexterity test in patients with PD (5, 45). The CR task requires the patient to rotate a 20 swiss cent through consecutive 180° half turns, as rapidly as possible for 10 rotations. Time to complete the 9-HPT and the CR tasks are recorded, by an experienced non-blinded outcome assessor ([name]), twice for each hand separately.

The subscale II of the MDS-UPDRS (41), containing 13 items, and each of them scored on a 0–4 rating scale (0 = normal; 1 = slight problem, 2 = mild problem, 3 = moderate problem, 4 = severe problem), is used to assess improvements on overall ADL. The scale is designed to be a self-administered questionnaire, but can be reviewed by the outcome assessor to ensure completeness and clarity.

To assess QoL (at T0, T1, and T2), we used the Parkinson's disease questionnaire-39 (PDQ-39) (46). This patient self-rated questionnaire consists of 39 questions, which are divided into eight subscales (mobility, ADL, emotional well-being, stigma, social support, cognition, communication, and bodily discomfort). The total score is given by the sum of all items and is then transformed in a range from 0 to 100. A lower value corresponds to a better perception of subject's QoL.

### Stimulation Protocol

iTBS is applied using a MagPro R30 stimulator (Medtronic Functional Diagnostics, Skovlunde, Denmark), connected to a figure-of-eight coil (Magnetic Coil Transducer MC-B70, Medtronic) with an outer radius of 50 mm or to a similar looking sham coil (Magnetic Coil Transducer MC-P-B70, Medtronic). An iTBS protocol is used as done in our previous rTMS study (4). For the iTBS protocol a theta burst of three pulses with a 20-ms interval repeated as a train of 10 bursts with a repetition rate of 5 Hz is used. Trains are repeated 20 times with an interval of 8-s. During stimulation, the examiner places the figure-eight coil over the left or right SMA, depending on the side of the more severe dexterity problems. The position for SMA stimulation is determined in each patient as follows. First, the optimal position for activation of the right abductor hallucis muscle will be determined by moving the coil in 1 cm steps along the sagittal midline around scalp vertex (Cz) with the handle pointing to the right. The active motor threshold (AMT) for this muscle is then determined. Next, stimuli at 120% AMT are given, moving the coil anteriorly along the sagittal mid-line in 1 cm steps. The SMA is defined as being 1 cm anterior to the last site from which motor evoked potentials (MEPs) can be evoked during contraction (47). Following these criteria, the position for SMA stimulation is expected to be 3 cm anterior from the optimal position for activation of the abductor hallucis muscle in most patients. Sham stimulation is applied by the same iTBS protocol, however a sham coil is used. The patients are asked to keep their eyes closed during stimulation. Immediately after stimulation the PD patients start with the VBT.

### VBT Intervention

The VBT intervention takes place at the neurorehabilitation outpatient center, Lucerne Cantonal Hospital. The interactive training program contains the use of two different devices. Each device is used for about 15 min. The first interactive device is the GripAble (https://gripable.co/) (Figure 2A), which is a new wireless device allowing the training of upper-arm and hand movements during wrist extension and flexion, pronation and supination, wrist radial and ulnar deviation, and also hand and pinch grip-force (48). To be able to manipulate objects well-one needs good hand/finger pinch grip and release (49, 50). The device is able to capture fine hand/finger movements. It can be connected (by bluetooth) with a tablet on which a GripAble app including different therapy games is installed. So far, nine games are available, of which five were chosen to be used for the present trial, since each of these five games focus on different hand/finger movements. Finger movements (pinch grip) can be done by adding a pinch pin.

**Figure 2 F2:**
[figure not shown]
Video based training with GripAble. Top left **(A)** GripAble device; top middle **(B)** Plume; top right **(C)** Windowsill; bottom left **(D)** patient playing Balloon Buddies; bottom middle **(E)** Circus Escape; bottom right **(F)** Pufferfish.

#### Plume

In this activity, the user is controlling the bird as it flies along a course using wrist flexion to move downward and wrist extension to move upward. The patient has to collect as many feathers as possible and to avoid different obstacles. If the bird flies in an obstacle the patients lose points. High level of visual perception and concentration is required. The time taken increases as the user works through the levels (Figure 2B top middle).

#### Windowsill

This activity requires wrist pronation, supination, and grip release. This activity presents pots in different places on a windowsill. A bag of soil is then moved left to right (using pronation/supination) until it is placed directly above one of the pots. When still, the soil can be released to fill the pot by gripping. Once the pot is full, a seed can be placed into the pot using the same control. This is followed by a watering can which needs to be poured until the flower appears. As the levels progress, more pots appear and are at a wider spacing (Figure 2C top right).

#### Balloon Buddies

The focus is on controlled grip (requiring hand/finger strength and endurance) and release. The patient controls an owl which is suspended from the balloon. The owl needs to collect all the stars to gain points. Squeezing GripAble inflates the balloon to make the owl go up the screen. Releasing GripAble brings the owl down the screen. The levels give increased time and complexity of the required control. The emphasis is on smooth transition between grip and release. The placement and the smoothness of the curve of stars alters through the levels to give gradual increase in demand (see Figure 2D bottom left).

#### Circus Escape

This activity targets controlled and fast reaction in grip and release. The goal is for the patients to power the bear on the cycle along the course without falling off the cliff. The patient will need to squeeze with more intensity and harder as the cycle moves up hills. The levels increase in complexity and length as they progress. There is a natural break within each level as the user waits for the hazards to reach the point of safe movement (Figure 2E bottom middle).

#### Pufferfish

This activity requires wrist ulnar and radial hand deviation, optional grip and release. The patient is controlling the fish to move up and down the screen by moving GripAble through wrist radial and ulnar deviation. The fish needs to catch the bubbles. In Level 3 onwards, hazards appear which need to be avoided or can be blown away by squeezing. The fish will not be affected by swimming over the sandy area at the base of the screen (Figure 2F bottom right).

The second device is the Leap Motion™ Controller, LMC™ (https://www.leapmotion.com/) which is an optoelectronic commercially available device suitable for hand gesture-controlled user interfaces allowing human–computer interaction. It tracks hand and finger movements by modelling all physiological hand and finger joints within a virtual reality (VR) environment (51, 52). The patients see their hand in real time on the screen (Figure 3).

**Figure 3 F3:**
[figure not shown]
Leap Motion training, Top left **(A)** Blocks; top right **(B)** flower; bottom left **(C)** Tilt Your Ball; bottom right **(D)** Fragmented 3D.

Four games were downloaded from the manufacturer's Web site (Leap Motion Gallery: Blocks, Flowers, Tilt Your Ball and Fragmental 3D (see also https://gallery.leapmotion.com/), which were partly evaluated in our previous pilot study (14). In short, in the first game, *Tilt Your Ball* (Figure 3A top left), the screen shows a room filled with four colored blocks. There are also four bodies. The aim is to use the fingers to connect the colored blocks to the body (pinch grip). The second game shows a flower (Figure 3B top right) made of steel with seven pedals. The aim is to remove the pedals one by one with the fingers. In *Tilt Your Ball* (Figure 3C bottom left), the patient has to navigate a small metal ball through different levels by tilting his hand. The successive levels become more and more difficult. *Fragmented 3D* (Figure 3D bottom right) is played by moving, rotating, and dropping blocks to form rows across a 3D grid. The goal is to build rows across the grid to erase lines, make combos and thus score points. The games Blocks, Flower, Fragmented 3D specifically requires fine coordinated movements. Tilt Your Ball requires fine combined wrist flexion extension, forearm prosupination movements, which are all needed for optimal object manipulation.

### Statistical Analysis

Descriptive statistics are used to present baseline characteristics and results of outcome measurements. In order to investigate the treatment effect for the primary endpoint, a hierarchical testing strategy is applied. For DextQ-24 at T1, an ANCOVA model is used with a fixed effect for treatment and the baseline (T0) value of DextQ-24 as a covariate. If a treatment effect at T1 could have been shown (null hypothesis rejected), the same approach will be performed for DextQ-24 at T2 in order to see whether the treatment effect is sustainable. An estimate for the treatment effect will be derived from the model together with a corresponding 95% confidence interval. As a postestimation procedure effect size measures such as (partial) eta square with corresponding 95% intervals will be provided. In an exploratory manner, the secondary endpoints are tested utilizing the same methodology. As a sensitivity analysis, e.g., to explore the robustness of the results in case of missing values, the primary and secondary endpoints are analyzed using linear mixed effects models with fixed effects for treatment, time point, interaction of treatment and time point, baseline value as a covariate and with subject as a random effect. Estimates for the treatment effects at T1 and T2 with corresponding 95% confidence intervals can be obtained as contrasts derived from these models. Further supportive analyses to check the robustness of the treatment effect estimators can be performed by adjusting the model from the primary analysis for the stratifying variable, namely the H&Y scale.

According to the treatment policy strategy (Intention to treat (ITT) principle) every randomized PD patient, including the drop-outs, is included for final evaluation. For all analyses the level of significance is set to alpha = 0.05 (two-tailed). Statistical analyses are performed using Stata (Version 16.1 or later, StataCorp, College Station, Texas, USA).

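### The sensitivity mixed model shares one baseline slope and, as usually read, one variance across T1 and T2, so its visit-specific intervals are miscalibrated if the visits differ

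*Protocol article*

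**What the plan says.** The Statistical Analysis section tests the primary endpoint visit by visit: "For DextQ-24 at T1, an ANCOVA model is used with a fixed effect for treatment and the baseline (T0) value of DextQ-24 as a covariate". The same ANCOVA follows at T2 only when T1 is significant. Each of these fits has its own baseline slope and its own residual variance.

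The mixed model is introduced separately: "As a sensitivity analysis, e.g., to explore the robustness of the results in case of missing values". It is described as "linear mixed effects models with fixed effects for treatment, time point, interaction of treatment and time point", with "baseline value as a covariate and with subject as a random effect". Its output is visit-specific: "Estimates for the treatment effects at T1 and T2 with corresponding 95% confidence intervals can be obtained as contrasts derived from these models". It applies to the primary and the secondary endpoints. The residual covariance structure, the estimation method and the degrees of freedom are not stated.

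**The concern.** Time point interacts with treatment but not with baseline, so one baseline slope serves both follow-ups. A subject random effect, read in the ordinary way, adds one between-patient variance and one residual variance, both common to T1 and T2. The visit-wise ANCOVAs impose neither restriction.

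Two things follow. First, the T1 and T2 contrasts share a pooled standard error. If the spread around the baseline regression differs between visits, that standard error is too large at one and too small at the other. Randomisation protects the point estimates but not the intervals. Second, the model changes the slope and variance assumptions as well as the handling of missing values. A gap between it and the ANCOVA is therefore not purely a missing-data effect, although exploring missing data is the purpose given for it.

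The T2 interval deserves attention because the mixed model yields a T2 estimate whether or not the T1 test rejects, and long-term benefit is one of the trial's main aims.

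**Working it through.** **Inputs from the article.** 30 evaluable patients, 15 per group; within-group SD up to 10 points, one figure for all visits; two-sided alpha 0.05; follow-up at 3 weeks and 3 months. The plan's own sample size reproduces: a two-sample t-test at 1.1 SD needs 15 per group (power 82.8%), and 30/(1 − 0.15) = 35.3, rounded up to 36.

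**Assumed, because the article gives no figures.** Correlations between T0, T1 and T2; SD 10 at every visit; complete data; no true effect.

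**Why the standard error is common.** With two visits and complete data, the random-intercept model splits into a regression of the patient mean on treatment and baseline and a regression of the patient difference (T2 − T1) on treatment alone. Each visit's treatment effect is the mean effect plus or minus half the difference effect. Its variance is proportional to Var(mean) + Var(difference)/4 = (V1 + V2)/2 at both visits, where Vk is the variance at visit k around the common slope.

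With equal SDs the slope at visit k equals its correlation with baseline, ρk, and the common slope is close to the average. So Vk = 100(1 − ρk²) + 100((ρ1 − ρ2)/2)².

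**Worked example, ρ1 = 0.8 and ρ2 = 0.6.**
- V1 = 36 + 1 = 37 and V2 = 64 + 1 = 65.
- Pooled value = (37 + 65)/2 = 51.
- Model SE over true SE: √(51/37) = 1.17 at T1 and √(51/65) = 0.89 at T2.

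The T1 interval is thus about 17% too wide and the T2 interval about 11% too narrow.

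**Null rejection by simulation** (20,000 trials per row, REML-type variances, t on N − 3 = 27 degrees of freedom, nominal 5%):

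| Assumed T0–T1, T0–T2, T1–T2 | Mixed model T1 | Mixed model T2 |
|---|---|---|
| 0.7, 0.6, 0.7 | 3.6% | 5.8% |
| 0.8, 0.7, 0.75 | 2.9% | 6.5% |
| 0.8, 0.6, 0.7 | 2.0% | 7.7% |
| 0.85, 0.6, 0.7 | 1.3% | 8.8% |
| 0.9, 0.7, 0.75 | 0.8% | 9.8% |
| all equal (0.7 or 0.8) | 4.6–4.7% | 4.6–4.7% |
| 0.6, 0.8, 0.7 (order reversed) | 7.6% | 2.3% |

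Visit-wise ANCOVA stayed at 4.7–5.2% in the rows where T0–T1 exceeds T0–T2.

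**Second parametrisation** (6,000 trials, normal-based intervals). With residual SDs of 6 and 9 and slopes of 0.8 and 0.6, the mixed model's interval is 11.1 points wide at both visits, against 9.0 (T1) and 13.6 (T2) from separate ANCOVAs. Its coverage is 98.4% and 90.2%. Swapping the visits gives 89.8% and 98.0%.

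**Agreement with the ANCOVA when nothing is missing.** The two T1 estimates differ by (ANCOVA slope − common slope) × chance baseline imbalance. The SD of that imbalance is 10√(1/15 + 1/15) = 3.65. In the example the slope gap is 0.8 − 0.7 = 0.1, which alone gives 0.1 × 3.65 = 0.37 points. With sampling error in the slopes, the simulated SD of the difference is about 0.3–0.5 points where the correlations differ.

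**The case against.** **Direction.** A reader might infer that the intervals will be too wide at T1 and too narrow at T2, because T1 lies closer to baseline. The article does not support this as a fact: it gives one SD and no visit-specific correlation. The other order is also plausible. Both arms train between T0 and T1, and the Introduction and Discussion report short-term but no lasting effects of earlier dexterity training. If response varies between patients and then fades, T2 may resemble T0 more than T1 does. The MDC95 of 8 with SD 10 implies a reliability near 0.92 (SEM = 8/(1.96√2) = 2.89; 1 − 0.289² = 0.917). That speaks to short-term repeatability, not to decay across an intervention. This objection stands, so the direction has to be conditional.

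**Role of the model.** It is tempting to call this the only analysis that uses patients with one missing follow-up, and so the sole support for the statement that "every randomized PD patient, including the drop-outs, is included for final evaluation". That is wrong. A patient with T1 but no T2 is in the primary T1 ANCOVA, and the Sample Size section encourages drop-outs to provide at least T1. A patient with neither visit is in no model, including the one proposed here.

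**Consequence.** This is a sensitivity analysis; the confirmatory tests are the ANCOVAs. Nor would it hide a short-term effect of the planned size: with a true 10-point difference its T1 power is 94%, 97% and 99.9% for (0.7, 0.6, 0.7), (0.8, 0.6, 0.7) and (0.9, 0.7, 0.75), against 95%, 99% and 100% for ANCOVA. An estimate gap of 0.3–0.5 points is also small beside a 10-point target.

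**Unstated detail.** Covariance structure, REML or ML, and degrees of freedom are often left to an analysis plan that is not shown. Higher error rates under maximum likelihood with normal-based tests would rest on a fitting choice that the article does not make, so they are not counted here. What remains is what the article does fix: a model with one baseline slope and a subject random effect.

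**Conclusion.** The point holds in conditional form. As specified and ordinarily read, the sensitivity model gives T1 and T2 one baseline slope and one variance. If the visits differ in either respect, its visit-specific 95% intervals are miscalibrated: too wide at the less variable visit and too narrow at the more variable one.

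Under assumed correlations with T0–T1 above T0–T2, null rejection is about 1–3.5% at T1 and 6–10% at T2. With equal correlations the problem disappears, and with the order reversed so does the pattern. All these sizes assume 15 per arm, SD 10, complete data and a random intercept with constant residual variance. The imperfect match with the ANCOVAs does not depend on which visit is more variable, but it is small.

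The primary tests keep their 5% level. This is a matter to consider, not a threat to the trial's main conclusion.

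**What to change.** Respecify the sensitivity model as a repeated-measures model for T1 and T2 with treatment, time point, treatment by time point, baseline and baseline by time point. Use an unstructured 2x2 within-patient residual covariance in place of the random intercept, and fit by REML with small-sample degrees of freedom such as Kenward-Roger, which the planned software offers.

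With complete data, both visits then have the same regressors and their own variance, so the T1 and T2 estimates equal those of the two ANCOVAs. A difference between the analyses then reflects missing data. The model is suitable whichever visit turns out more variable.

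The cost is a change to one model specification and two extra parameters (one slope, one variance) with about 30 patients. With only two visits, convergence should not be a difficulty. The primary analysis and the sample size stay as they are.

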## Methods and Analysis

### Trial Design

A single-blind (patients) parallel RCT with a stratified random intervention distribution is carried out. The random sequence generation using a computer software program is stratified, according to the Hoehn & Yahr (H&Y) scale, Level 1 = H&Y I to Level 4 = H&Y 4, (36) at T0. After stratification, a simple randomization (1–1) occurs within each stratum level (Level 1 to 4). Randomization and treatment allocation is concealed within SecuTrial, which is a GCP-compliant electronic data base system (https://www.secutrial.com/en/), managed externally by the Clinical Trial Unit (CTU) Schweizer Paraplegiker Zentrum (SPZ) Nottwil. After the baseline assessment (hereinafter referred to as T0), all PD patients receive 45-min manual dexterity intervention three times a week for a period of 3 weeks. The PD patients randomized in the experimental group will receive VBT each time, preceded by true iTBS stimulation. The PD patients randomized to the control group receive a VBT with a preceding sham TMS each time (see Figure 1). Patients will be blinded to the rTMS protocol (sham vs. real). This means that patients will not be informed throughout the whole trial whether they received real or sham rTMS stimulation. Follow-up measurements (T1 and T2) are carried out after a period of 3 weeks and 3 months. All data is collected within SecuTrial. The study will be performed according to the CONSORT (Consolidated Standards of Reporting Trials) statement, http://www.consort-statement.org/.

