### Sample Size Calculation

The significance level alpha is defined as 0.05 (two-tailed) for detecting a mean difference between groups on the primary outcome being the Dexterity Questionnaire 24 (DextQ-24) (4) in favor of the real iTBS-VBT dexterity group. Based on previously observed data one may assume a within-group standard deviation of up to 10 points. The study is designed to detect a mean difference of 10 or more points, which exceeds the MDC95 of 8 points found in our validation study (4). A total sample size of 30 evaluable subjects, 15 per group, is required to detect a mean difference of an at least 1.1-fold within-group standard deviation with a target power of at least 80%. Considering a maximal drop-out rate of 15%, we aim to recruit 36 patients in total.

In any case, patients who do not complete the training sessions and/or even decide to drop out of the study for whatever reason will be encouraged to continue to participate in the scheduled assessments for at least T1 (and/or a time point prior to the individual end of the study) and ideally to provide a postbaseline assessment for at least the primary endpoint.

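### The primary ANCOVA omits H&Y, the stratification factor, and leaves adjustment for it optional and of unspecified form; one prespecified term would be a cheap improvement

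*Protocol article*

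**What the plan says.** Under Trial Design, the protocol article says: "The random sequence generation using a computer software program is stratified, according to the Hoehn & Yahr (H&Y) scale". There are four levels, H&Y I to IV. It then says how patients are allocated inside them: "After stratification, a simple randomization (1–1) occurs within each stratum level (Level 1 to 4"). No blocking or other restriction is stated.

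Under Statistical Analysis, the primary comparison of DextQ-24 at T1 is fixed: "an ANCOVA model is used with a fixed effect for treatment and the baseline (T0) value of DextQ-24 as a covariate". If that test rejects, "the same approach will be performed for DextQ-24 at T2 in order to see whether the treatment effect is sustainable". The secondary endpoints follow the same method on an exploratory basis. The mixed-model sensitivity analysis has "fixed effects for treatment, time point, interaction of treatment and time point, baseline value as a covariate and with subject as a random effect". None of these models contains H&Y.

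H&Y appears once in the analysis section, in further supportive analyses that "can be performed by adjusting the model from the primary analysis for the stratifying variable, namely the H&Y scale". The article does not say whether H&Y would enter as a linear score, in groups or as four categories. It gives no reason for leaving the factor out of the primary model.

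**The concern.** A factor used to stratify randomisation normally belongs in the primary model. Here it is recorded for every patient before allocation, so using it needs no new data, yet the analysis treats it as an afterthought.

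Two things are at stake. The first is precision: with 30 evaluable patients planned, any outcome variance that H&Y explains beyond the baseline score stays in the error term. The second is chance imbalance. Simple randomisation carried out separately in each stratum amounts to simple randomisation overall, so the stratification as written does nothing to equalise severity between arms. Only the analysis can correct for it, and the primary analysis does not.

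A lesser matter is the wording. The adjusted analysis may or may not be run, and its form is open.

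**Working it through.** **The plan's own figure.** Inputs from Sample Size Calculation: two-sided alpha 0.05, a standardised difference of 1.1, power of at least 80%, 15% drop-out. A two-sample t test (noncentral t) needs 14.002 per group, so 15 per group and 30 in total, with power 82.8%. Then 30 / (1 − 0.15) = 35.3, so 36. The stated 30 and 36 are reproduced. The calculation is consistent with a two-group comparison without covariates, so adding H&Y to the model changes neither number.

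**Validity of the planned test.** The unadjusted ANCOVA was simulated at N = 30 with SD 10, which is the upper figure in the article ("one may assume a within-group standard deviation of up to 10 points"), and simple allocation. Assumptions: H&Y mix 15/45/30/10% for stages I to IV, correlation of baseline with outcome 0 or 0.5, and H&Y explaining 0%, 10% or 30% of residual variance. Type I error was 5.0% to 5.5% in every scenario (5,000 runs each), so the nominal level holds.

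**If allocation is in fact blocked.** With blocks of 4 within strata (an assumption; the article states none), the unadjusted test is conservative:

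- H&Y explains 10% of residual variance: type I error 3.9% to 4.8%.
- H&Y explains 30%: 2.5% to 2.8%.
- The adjusted tests stay at 4.7% to 5.8% at both values.

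**Chance imbalance under the allocation as written.** This is the share of simulated trials in which the arms differ by at least 20 percentage points in H&Y III-IV. The proportion in III-IV is an assumption, because the article gives none.

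| Patients in III-IV | N = 30 | N = 36 |
|---|---|---|
| 20% | 19% | 14% |
| 30% | 25% | 20% |
| 40% | 29% | 24% |
| 50% | 30% | 25% |

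If III-IV patients score 5 points worse at T1 for equal baseline (assumption), a 20-point imbalance moves the unadjusted estimate by 0.20 × 5 = 1 point.

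**Precision.** The planned model estimates three coefficients and leaves 30 − 3 = 27 degrees of freedom. One H&Y term leaves 26. The approximate variance ratio, adjusted to unadjusted, is (1 − R²) × 27/26, where R² is the share of the variance left after baseline that H&Y explains.

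| R² (assumed) | Ratio | Change in variance |
|---|---|---|
| 0 | 1.038 | about +4% |
| 5% | 0.987 | about −1% |
| 10% | 0.935 | about −7% |
| 20% | 0.831 | about −17% |

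Break-even is R² = 1 − 26/27 = 3.7%.

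**Power.** Simulation at N = 30 with a 10-point effect, SD 10, baseline correlation 0.5, simple allocation and the same H&Y mix (3,000 runs each):

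| R² (assumed) | No H&Y | H&Y linear | H&Y four categories |
|---|---|---|---|
| 0 | 83% | 81% | 78% |
| 10% | 84% | 86% | 83% |
| 30% | 84% | 94% | 92% |

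The linear term loses about 2 points at worst. Four categories lose about 5, which is why one term is preferable in a trial of this size.

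**The case against.** The strongest reply is that the primary analysis is sound as it stands. The test keeps its level. Chance imbalance under randomisation is not bias, and the planned confidence interval already allows for it. Baseline DextQ-24 is the same scale as the outcome and may absorb much of what H&Y predicts. The article gives no figure for what remains. All of this stands.

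The gain may also be small. Take the 5-point illustration with 40% in III-IV and SD 10. H&Y then explains 25 × 0.4 × 0.6 / 100 = 6% of the variance left after baseline if the baseline correlation is 0. Dividing by 1 − 0.5² gives 8% at correlation 0.5, and dividing by 1 − 0.7² gives 12% at 0.7. By the formula above, the variance falls by about 2%, 4% and 8%. The 1-point shift is about 0.3 of a standard error: 10 × √(1 − 0.5²) × √(2/15) = 3.2 points at correlation 0.5. It is also one tenth of the 10-point target. A sparse model for about 30 patients is defensible, although the article does not argue for it.

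Three stronger readings are tempting, and the document does not support them:

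- **The planned standard errors are too wide.** That needs allocation balanced within strata, and the article states simple randomisation there.
- **There are two competing primary estimates.** The article names one primary model and labels the H&Y model supportive. What is open is whether that supportive model is run, and in what form.
- **The investigators judged H&Y strongly prognostic.** The article gives no reason for stratifying on it.

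What remains is an asymmetry. The worst case of adding one term is a rise of about 4% in variance. The possible gain is several times that, and the term also corrects for an imbalance that the allocation does nothing to prevent.

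**Conclusion.** The point holds as a cheap improvement and not as an error. H&Y stratifies the randomisation but is absent from the primary ANCOVA, the models that follow it and the mixed model, and its supportive use is optional and unspecified. No stated figure is wrong on this point, and type I error is about 5% under the allocation as written.

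The benefit is a fall in variance of about 1%, 7% or 17% if H&Y explains 5%, 10% or 20% of what baseline leaves, against a rise of about 4% if it explains nothing. It also corrects the estimate for a severity imbalance of 20 percentage points or more, which occurs in about 14% to 30% of trials of 30 to 36 patients when 20% to 50% are in III-IV. The H&Y mix, the R² values and the 5-point gap are assumptions. If the database in fact allocates in blocks within strata, the case is stronger, because the unadjusted test would then be conservative.

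**What to change.** Prespecify the primary model for DextQ-24 at T1, and then at T2 under the existing hierarchy, as treatment + baseline DextQ-24 + H&Y, with H&Y as a single linear term scored 1 to 4. One linear term avoids separate coefficients for stages that may be sparse. Carry the same term into the secondary-endpoint ANCOVAs and the mixed models. Make the model without H&Y the supportive analysis, and state that it will be reported.

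The cost is one sentence of analysis wording and one degree of freedom, with about 2 points of power lost if H&Y proves uninformative. No new data are needed, and the sample size is unchanged.
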